##### Midpoint estimated glomerular filtration rate

The null hypothesis is that the population mean of the midpoint eGFR in the intervention group is the same as that in the placebo group (after adjustment for baseline eGFR). The alternative hypothesis is that the population mean of the midpoint eGFR is higher in the intervention group, compared to that in the placebo group (after adjustment for baseline eGFR).

#### Exploratory concepts

The exploratory outcomes (summarised in Supplementary Table 1) taken at the end of the treatment period will be compared between the treatment and placebo groups (adjusting for the values taken at the beginning of the treatment). These will be carried out as exploratory analyses to inform future research directions.

#### Safety objectives

The safety objectives are to assess the effects of the GKT137831 compared to placebo on the key safety outcome measures (treatment-emergent adverse events and abnormal laboratory analytes) and the other safety outcome measures defined in “Safety outcome measures” section.

### Analysis methods

#### Primary analyses

##### Main analysis model

The main analysis will be based on the ITT analysis set. The analysis model will be a linear mixed effects model with endpoint UACR (log-transformed) as the outcome, a categorical variable indicating the allocated grouping structure (intervention versus placebo) as the exposure, and a random effect term to account for the study centre variability. The model will incorporate other covariates as discussed in “Covariate adjustment” section. The results from this analysis will be summarised in Table 3.

**Table 3 Tab3:** Primary and secondary results of the GKT137831 trial

Outcome		Analysis	Mean (standard deviation)		Estimated mean difference^a^	95% Confidence Interval	*P* value
			Intervention (GKT137831) group (n = xxx)	Placebo group (*n* = xxx)			
Primary	Endpoint UACR	Intention to treat (ITT)					
		modified ITT					
		Per protocol (PP)					
Secondary	Midpoint UACR	Intention to treat (ITT)					
		modified ITT					
		Per protocol (PP)					
	Endpoint eGFR	Intention to treat (ITT)					
		modified ITT					
		Per protocol (PP)					
	Midpoint eGFR	Intention to treat (ITT)					
		modified ITT					
		Per protocol (PP)					

*UACR*  urine albumin: creatinine ratio, *eGFR* estimated glomerular filtration rate

^a^ In the intervention group compared to placebo

##### Covariate adjustment

The main analysis model described in “Main analysis model” section will include (log-transformed) baseline UACR as a covariate. To assess potential baseline covariate imbalance, the participant characteristics at baseline described in “Baseline participant characteristics” section will be compared between the intervention and placebo arms. Instead of using hypothesis testing for this purpose due to its dependence on sample size and emphasis on statistical significance, the standardized differences in means or proportions [8] will be used. The main analysis model will also include the baseline variables that have values of 10% or greater, in the magnitude of the percentage standardised differences, as covariates*.*

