### Randomisation

The randomisation ratio is 1:1 between the active drug (GKT137831) and placebo control arms, and is stratified by study centre and urinary albumin–creatinine ratio (UACR) level with the grouping defined as ≤ 35 mg/mmol or > 35 mg/mmol in female participants and ≤ 25 mg/mmol or > 25 mg/mmol in male participants using a minimisation strategy [4]. Participants will be randomised using a minimisation program integrated into the Interactive Web Response System, and is accessed live by sites through the website Randomize.net (see Sect. 3.3 of the protocol [2]).

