### Sample size

Up to 284 participants in total are expected to be screened (anticipated screen fail rate up to 50%) with 142 participants each randomised to the treatment and placebo groups, to achieve 120 participants reaching the end of the treatment period in total (60 per treatment group). Sect. 2.5 of the protocol [2] provides details of the sample size calculations. In brief, the assumptions of the sample size calculations were the following: mean UACR of 13.56 mg/mmol in the control arm, difference between UACR means in the treatment arm of 3.56 mg/mmol/L (26% reduction in mean UACR in the treatment arm), equal standard deviations of 7.5 mg/mmol in the two arms, and within-subject correlation of 0.3. Using mixed model analysis of covariance with log-transformed UACR as the outcome, several scenarios were examined: 60 participants per treatment arm are required to achieve power > 90% with an alpha level of 0.05 and two-sided hypothesis testing, and 40 participants per treatment arm are required to achieve power > 90% with an alpha level of 0.05 and one-sided hypothesis testing.

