### Baseline participant characteristics

The characteristics of the participants, will be summarised by study arm and overall at baseline using summary statistics as shown in Table 2. Continuous variables will be summarised by the appropriate central tendency and dispersion measures, using either mean and standard deviation (SD) or median and 25th–75th percentile. Categorical data will be summarised using frequencies and percentages. The frequencies and percentages of missing values will be reported for all variables.

**Table 2 Tab2:** The baseline characteristics of the participants by intervention, placebo groups and overall

Baseline characteristic	Intervention (GKT137831) group (*n* = xxx)		Placebo group (*n* = xxx)		Percentage standardised difference	Overall (*n* = xxx)	
	Values	Missing, *n* (%)	Values	Missing, *n* (%)		Values	Missing, *n* (%)
**Urine albumin–creatinine ratio (UACR)** (log-transformed)							
Mean (standard deviation (SD))							
**Estimated glomerular filtration rate (eGFR)** (log-transformed)							
Mean (SD)							

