##### Sensitivity analyses

The results obtained by using a mixed effects model of the (log-transformed) endpoint UACR with the allocated grouping structure as the exposure, a random effect term to account for the study centre variability, only incorporating (log-transformed) baseline UACR as a covariate without additional baseline covariates will also be made available. In addition, the sensitivity of the results to the decisions made in constructing the imputation model, will be investigated using visualisations of the distributions of imputed and observed values, standard regression diagnostics [17], and comparisons with complete case analysis. The results will be presented as outlined in Fig. 2.

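### The primary model's extra covariates are chosen by a 10% imbalance rule that chance alone triggers for more than half of the candidates; the cost is modest and conservative, but the covariates should be named now

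*SAP article*

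**What the plan says.** - **SAP, Main analysis model.** The ITT model for log endpoint UACR has treatment, "a random effect term to account for the study centre variability. The model will incorporate other covariates", with those covariates deferred to the next section.
- **SAP, Covariate adjustment.** The model "will include (log-transformed) baseline UACR as a covariate". The baseline characteristics "will be compared between the intervention and placebo arms" by standardised difference, and the main model "will also include the baseline variables that have values of 10% or greater, in the magnitude of the percentage standardised differences". No other covariate is named.
- **SAP, Baseline participant characteristics.** The candidates are the characteristics that "will be summarised by study arm and overall at baseline using summary statistics as shown in Table 2". Besides UACR there are 11: eGFR, gender, age, ethnicity, systolic and diastolic pressure, ACE inhibitor use, ARB use, BMI, diabetes duration and HbA1c.
- **SAP, Sensitivity analyses.** A model "only incorporating (log-transformed) baseline UACR as a covariate without additional baseline covariates" is also to be reported.
- **SAP, Randomisation.** Allocation "is stratified by study centre and urinary albumin–creatinine ratio (UACR) level" by minimisation, with UACR cut-offs that differ by sex.

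**The concern.** A covariate earns its place in a randomised comparison by predicting the outcome. Here it earns its place by the size of its observed imbalance, which under randomisation is chance.

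- **The primary model is not fixed.** With 11 candidates there are 2^11 = 2,048 possible covariate sets, and which one applies is settled only when baseline data are divided by arm.
- **Precision is left to luck.** A prognostic variable that happens to balance is omitted, and an irrelevant one that happens not to balance is included. Related variables such as systolic and diastolic pressure may enter together.
- **There are knock-on effects.** The Missing data section uses multiple imputation when covariates have missing values but not when only the outcome does, so a chance inclusion can change how missing data are handled. The analysis is repeated for the modified ITT and PP sets and for secondary outcomes, without saying whether the selection is redone. Rows of Table 3 could then carry different covariates.

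The SAP rejects baseline hypothesis tests partly because they depend on sample size. A fixed 10% cut-off has the same weakness: how often chance triggers it also depends on sample size, as shown below.

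**Working it through.** **Inputs.** The Sample size section plans "to achieve 120 participants reaching the end of the treatment period in total (60 per treatment group"). It also gives 284 screened and up to 50% screen failure: 284 × 0.5 = 142 randomised, or 71 per arm, with 1 − 120/142 = 15.5% loss before the end of treatment. Its wording can be read as 142 in each arm, so that case is shown too.

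**The plan's own figure.** The SAP gives no trigger rate for the rule. Its power statement can be reproduced. Converting means of 13.56 and 10.00 with SD 7.5 to log scale gives log SDs of 0.517 and 0.668 and a difference of 0.394. Power is then 95.1% unadjusted and 96.6% with baseline adjustment (60 per arm, two-sided), and 90.4% and 92.6% (40 per arm, one-sided). Other conversions give less. This point does not depend on which was used.

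**Chance trigger rate.** With no true imbalance, a standardised difference d is approximately normal with mean 0 and SE = sqrt(2/n), n per arm. So P(|d| ≥ 0.10) = 2 × [1 − Φ(0.10/SE)].

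| n per arm | SE | 0.10/SE | P per variable | Expected of 11 |
|---|---|---|---|---|
| 60 | 0.183 | 0.55 | 58.4% | 6.4 |
| 71 | 0.168 | 0.60 | 55.1% | 6.1 |
| 142 | 0.119 | 0.84 | 39.9% | 4.4 |

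The rate falls below one half only above about 91 per arm: 2 × (0.6745/0.10)² = 91. Simulation at 60 and 71 per arm gave 58% and 55% for continuous variables, and 56-65% and 53-56% for binary variables with prevalence 0.15 to 0.5. If the 11 variables were independent, the central 95% range would be 3 to 9 entering. Correlated variables would widen that range.

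**Consequence for the test.** The SAP gives no covariate effects, so these must be assumed. The simulation had 11 independent standard normal covariates, three of them with standardised slope 0.10 or 0.25 on the outcome; a baseline slope of 0.3 (the SAP's within-subject correlation) or 0.5; outcome SD 1; treatment effect 0.45 SD; a one-sided 5% test; ordinary regression without a centre term; and 20,000 trials per row.

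| n per arm | Covariate slope | Baseline slope | Power: baseline UACR only | Power: 10% rule | Power: the three named | Type I error: 10% rule |
|---|---|---|---|---|---|---|
| 60 | 0.10 | 0.3 | 81.8% | 79.5% | 81.9% | 5.1% |
| 60 | 0.10 | 0.5 | 88.3% | 86.3% | 88.6% | 4.7% |
| 60 | 0.25 | 0.3 | 82.2% | 83.7% | 88.2% | 4.4% |
| 60 | 0.25 | 0.5 | 88.1% | 90.8% | 94.2% | 3.8% |
| 71 | 0.10 | 0.3 | 86.8% | 85.3% | 87.2% | 5.0% |
| 71 | 0.10 | 0.5 | 92.3% | 91.2% | 92.8% | 4.9% |
| 71 | 0.25 | 0.3 | 87.3% | 89.7% | 92.6% | 4.5% |
| 71 | 0.25 | 0.5 | 91.8% | 94.8% | 96.7% | 4.4% |

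Against the three named covariates the rule loses 1.6 to 4.5 points, and no more than 3 in six of the eight rows. Its average standard error is accurate at slope 0.10 (within about 1%) and 4-6% too large at slope 0.25. Monte Carlo error on the type I figures is about 0.15 points, so 5.1% is not distinguishable from 5%.

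**The case against.** The best defence is that the rule is mechanical. Candidates, metric and threshold are all stated, and the outcome plays no part, so an analyst has little room to steer the covariates towards a favourable result. The baseline-UACR-only model is specified and will be reported, so readers can see what the added covariates do. All of this stands.

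It also rules out several stronger readings that a reader might infer:

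- **That covariates are chosen after unblinding.** The SAP gives no timing. The rule uses absolute differences in baseline data, so masked arm labels would suffice and it could be run before endpoint data exist. Masking would not stop it selecting on noise.
- **That it defeats the SAP's aim of minimising reporting bias.** That is too strong for an outcome-blind rule reported beside a fixed model.
- **That false positives are inflated.** The simulations show nominal or slightly conservative error.
- **That any prognostic variable may be lost.** Baseline UACR and centre are always in the model.
- **That the rule always costs precision.** Against baseline UACR alone it gained 1.5 to 3 points when the three covariates were moderately prognostic (slope 0.25) and lost 1 to 2.5 points when they were weak (slope 0.10). The consistent loss is against a list chosen for prognosis, and the comparison assumes that the list is well chosen.

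Leaving out the minimisation stratum is also a small matter. It is a sex-specific cut of a variable already in the model in continuous form, so what is missing is mainly sex.

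**Conclusion.** The point holds in limited form. At the planned size, the 10% threshold is 0.55 to 0.60 of one standard error, so each candidate enters by chance with probability 55-58%, about 6 of 11. This rests on reading the Sample size section as 142 randomised in total, which fits its screening and completion figures. At 142 per arm the rate would be 40%, which is still selection on noise, but then more than half would be wrong.

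The result is a primary model whose covariates are unknown until the data are split by arm and are unrelated to prognosis. The statistical harm is modest and, where there is miscalibration, conservative: about 1 to 3 points of power in most settings tried, a standard error 0-6% too large, and one-sided type I error of roughly 4-5%. These sizes depend on assumed covariate effects; the trigger rate does not. The plan should be changed, but the rule as written would not invalidate the primary result.

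**What to change.** Replace the imbalance rule in Covariate adjustment with a named list for the primary model:

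- log baseline UACR;
- study centre as a random effect;
- sex, because the minimisation cut-offs are sex-specific;
- a short list from Table 2 that the investigators choose on prognostic grounds, for example baseline log eGFR, HbA1c or systolic pressure. The SAP has no evidence on which of these predict UACR, so the choice is theirs.

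State that the same list applies to the ITT, modified ITT and PP sets. Keep the 10% standardised-difference model and the baseline-UACR-only model as sensitivity analyses.

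The cost is SAP wording, since every variable is already in Table 2. The downside is a few degrees of freedom if a chosen covariate proves weak. The change should be dated before anyone sees baseline data by arm.

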##### Checking assumptions in statistical models

The assumptions of linearity between the explanatory variables and the outcome, constant variance and independence of the errors, and normality of the error distribution will be checked using plots of observed values versus predicted values, residuals versus predicted values, residuals versus individual independent variables, and normal probability plots. These plots will also be used to detect any outliers.

##### Alternative methods to be used if distributional assumptions do not hold

The UACR levels used in the analysis model will be log-transformed. However, alternative transformations will be considered in the cases where the assumptions of constant variance or normality of the error distribution is violated. Non-linear terms will be incorporated to account for any non-linearity between the explanatory variables and the outcome. If it is verifiable that any of the outliers are due to data that are incorrectly measured or registered, these outliers will be removed. The remaining outliers will be accommodated using robust estimation of linear mixed effects models [9].

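### The primary model may be changed after its own residual plots are read, with no stated trigger and no statement that the log-scale fit stays primary

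*SAP article*

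**What the plan says.** In the SAP article, *Main analysis model* sets the starting point: "The main analysis will be based on the ITT analysis set", and "The analysis model will be a linear mixed effects model with endpoint UACR (log-transformed) as the outcome", with allocated group as the exposure and a random centre effect. *Covariate adjustment* adds log baseline UACR. The result goes into Table 3, which has one ITT row for endpoint UACR: one estimate, one interval, one p value.

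Two later sections under the same *Primary analyses* heading then bear on that model. *Checking assumptions in statistical models* lists plots from the fitted model, among them "residuals versus individual independent variables, and normal probability plots", and adds: "These plots will also be used to detect any outliers". *Alternative methods to be used if distributional assumptions do not hold* gives the responses:

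- Transformation (possible, not certain): "alternative transformations will be considered in the cases where the assumptions of constant variance or normality of the error distribution is violated".
- Functional form (definite): "Non-linear terms will be incorporated to account for any non-linearity between the explanatory variables and the outcome".
- Verified errors (definite): "If it is verifiable that any of the outliers are due to data that are incorrectly measured or registered, these outliers will be removed".
- All other outliers (definite): "The remaining outliers will be accommodated using robust estimation of linear mixed effects models".

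*Sensitivity analyses* offers a log-scale mixed model adjusted for baseline UACR only. *Additional analyses* and *Secondary analyses* carry the whole sequence over to the modified ITT and PP sets and to the secondary outcomes.

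**The concern.** These rules act on the primary analysis itself. They are not labelled as sensitivity analyses, and Table 3 has no second ITT row in which the unmodified log-scale fit would appear beside a modified one. The text gives no residual cut-off, no criterion for non-normality or unequal variance, no list of candidate transformations and no order of steps. It names no robust estimator or tuning constant, leaving that to a cited reference.

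Two things are at stake. First, several candidate primary p values exist, and the choice among them depends on outcome data. The *Introduction* and *Conclusion* say the SAP is there to minimise reporting bias. Second, verified errors are taken out first, so the values that a robust fit then down-weights are those not shown to be wrong. Some may be real, large changes in albuminuria. If they are commoner in one arm, the robust fit estimates something other than the difference in population means that *Primary hypothesis* sets out to test.

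**Working it through.** **1. The plan's own figure.** *Sample size* gives means of 13.56 and 13.56 - 3.56 = 10.00 mg/mmol, SD 7.5 in both arms, correlation 0.3, and power above 90% for 60 per arm (two-sided 5%) and for 40 per arm (one-sided 5%), on log UACR. Assuming lognormal values:

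- SD of log = sqrt(ln(1 + (SD/mean)^2)): control sqrt(ln(1 + (7.5/13.56)^2)) = 0.517; active sqrt(ln(1 + (7.5/10)^2)) = 0.668; pooled 0.597.
- Mean of log = ln(mean) - variance/2: 2.474 and 2.079; difference 0.394.
- 60 per arm, two-sided: 0.394/(0.597 x sqrt(2/60)) = 3.62; 3.62 - 1.96 = 1.66; power 95.1%.
- 40 per arm, one-sided: 0.394/(0.597 x sqrt(2/40)) = 2.95; 2.95 - 1.645 = 1.31; power 90.4%.
- Adjusting for baseline with r = 0.3 multiplies the SD by sqrt(1 - 0.09): 96.6% and 92.6%.

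The stated power therefore reproduces for the fixed log-scale model. This depends on the conversion. If the 26% is instead read as a ratio on the log scale with the control SD of 0.517, the baseline-adjusted values are 92.3% and 86.8%.

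**2. Effect of free choice on type I error.** 5,000 simulated trials per scenario, 60 per arm, one-sided 5%. Assumptions not in the documents: log SD 0.55, baseline correlation 0.6, no centre effect, no missing data. Three fits: least squares on the log scale, least squares on the square-root scale, Huber estimation (k = 1.345) on the log scale.

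| Errors, no treatment effect | Fixed log-scale | Huber if any standardised residual exceeds 3 | Smallest p of the three |
|---|---|---|---|
| Normal | 5.0% | 5.1% | 6.5% |
| t with 3 df | 4.6% | 5.1% | 7.3% |

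The simulation standard error is at most about 0.4 points. The inflation comes from the freedom to choose, not from robust estimation.

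**3. Effect of robust fitting on the estimate.** Same settings, normal errors, extremes in the active arm only (assumed mixtures).

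- Strong responders: -0.105 for all, a further -1.5 in 10%. True mean: -0.105 - 0.150 = -0.255. Log-scale fit -0.255 (1 - exp(-0.255) = 22.5% reduction); Huber -0.188 (17.1%). Rejection 83% against 66%.
- Sharp worseners: -0.304 for all, +1.8 in 8%. True mean: -0.304 + 0.144 = -0.160. Log-scale fit -0.159 (14.7%); Huber -0.237 (21.1%). Rejection 47% against 83%.

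Under the mechanical 3 SD trigger the rejection rates were 68% and 83%, close to those of Huber. A fixed trigger controls the error rate but does not restore the target of estimation.

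**The case against.** The SAP does name its methods in advance and ties changes to diagnostics, not to p values. Robust estimation does not itself inflate the error rate. In a separate run of 3,000 trials with normal errors, Huber changed the treatment estimate by a median of only 0.15 standard errors. Each participant's endpoint UACR is already a geometric mean of four samples, which damps single-sample extremes. The baseline-only log-scale model will be made available. All of this stands, and it limits the size of the problem. The 6.5-7.3% is a worst case that uses a square-root scale the SAP never mentions, and the one-arm mixtures are assumed.

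The baseline-only model is a partial safeguard. It is a sensitivity analysis, it may differ from the primary model in covariates, and it is not stated to be fitted without robust estimation.

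Some stronger readings are tempting but not supported:

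- *The choice is made unblinded.* The SAP does not say who reads the plots or whether arm codes are masked. The fitted model contains treatment, so the plots could separate the arms, but that is an inference.
- *The remaining outliers are real values.* Only verifiable errors are removed, so the remainder may mix genuine values with errors that cannot be verified.
- *The transformation will be switched.* It will only be considered.
- *The switch will often be triggered by chance.* With 120 normal residuals the chance of at least one beyond 3 SD is 1 - (1 - 0.0027)^120 = 28% (23% in the simulation, which used fitted residuals). But the SAP sets no such cut-off, and under that trigger the error rate stayed near 5%.
- *Participants drop out of the ITT set.* Down-weighting excludes nobody.

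**Conclusion.** The point holds as one of pre-specification with a possible effect on the estimate. The sections on checking assumptions and on alternative methods make the primary estimator depend on plots read by eye, set no trigger, and do not say that the log-scale fit remains primary. That rests on the text alone.

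The sizes rest on assumed settings. Error inflation is modest, about 1.5 to 2.3 points above 5% at worst. The shift in the estimate is potentially larger and can go either way, but only if genuine extremes are unequal between arms. The sharp-worsening case matters most, because down-weighting those participants makes the drug look better. The documents give no basis for saying how likely such imbalance is.

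**What to change.** State in *Main analysis model* that the log-scale linear mixed model, with all values not confirmed as data errors, is the primary analysis whatever the diagnostics show. Resolve suspected data errors before treatment codes are released. Move robust, re-transformed and non-linear fits to *Sensitivity analyses*, labelled as such, naming the robust estimator and its tuning. If unequal variance is a concern, pre-specify sandwich or bootstrap standard errors for the same coefficient. Apply the same wording to the modified ITT, PP and secondary analyses.

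An objective trigger applied to masked data is a lesser alternative: it would deal with the freedom of choice but not with the change in what is estimated.

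The cost is SAP wording, plus a somewhat wider primary interval if residuals are heavy-tailed. The planned power is unaffected, since it was calculated for the log-scale model.
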